##### **4.1.1.2 K-WOMAC(Korean version Western Ontario and McMaster Universities Osteoarthritis Index)**

K-WOMAC survey(11.4) consists of 24 questions total over 3 areas with 5 questions on pain, 2 questions on stiffness, and 17 questions on physical function. Subjects will directly record the symptoms of the knee within 48 hours before visit through the 5-point Likert scale('None'(0), 'Slightly'(1), 'Mild'(2), 'Severe'(3), 'Very severe'(4)).

##### **4.1.1.3 Patient Global Assessment**

Subjective severity of disease and overall improvement in osteoarthritis of the knee will be evaluated using the following 5 point rating scale by the subject for final evaluation of effectiveness.

- 5 : Very good
- 4 : Good
- 3 : No change
- 2 : Poor
- 1 : Very poor

##### **4.1.1.4 Frequency of Rescue drug Usage**

Check for ratio and amount of medication among subjects by checking administration of rescue drug distributed to subjects upon every visit excluding visit 1.

#### **4.1.2 Safety Assessment**

##### **4.1.2.1 Adverse Reactions**

Subjects shall be trained to voluntarily report on information regarding adverse events and the investigator shall check for adverse effects through interview and surveys conducted on regular and additional visits. Adverse event investigation includes occurrence and disappearance dates, severity and results of adverse event, actions taken related to test/control drug, cause-and-effect relationship with test/control drug, name of substance suspected aside from test/control drug, treatment and details regarding adverse effect.

##### **4.1.2.2 Pregnancy Test and Clinical Pathology Examination**

Evaluation of clinical pathology examination shall be conducted according to the clinical trial schedule at the laboratory of testing institution.

Clinical pathology examination is conducted on all subjects and evaluates overall health of the subject. Inclusion and exclusion criteria including pregnancy test and clinical pathology examination must all be checked prior to administration of investigational product.

Additional tests are permitted by decision of clinical trial physician aside from tests according to the schedule when necessary. However, tests can be omitted if there are test results within 4 weeks from visit 1.

Test items include the following.

- Hematologic test : WBC, RBC, Hemoglobin, Hematocrit, Platelets count, WBC Diffcount
- Blood chemistry test : Na, K, Ca, Cl, BUN, Creatinine, Uric acid, Total bilirubin, Albumin, Total protein, Creatine Kinase, ALT, AST, rGT, Alkaline phosphatase, glucose, Total cholesterol, Triglyceride
- Blood coagulation test : PT, aPTT(Conducted only during visit 1)
- Urine test : Protein, Glucose, Urobilinogen, WBC, RBC

- Pregnancy test : Urine hCG (Only for women of childbearing age)

Criteria for reporting abnormal test results as adverse event is as below.

- When test results are relevant to associated symptoms
- When test results require additional diagnostic tests or medical/surgical treatment
- When test results cause change in dosage of study drug, suspension of trial, additional treatment using significant co-administered drugs or non-medicated therapy
- When test results are considered to be an adverse event by the investigator or the client

Simple repetition of abnormal clinical pathology test without meeting any of the conditions above is not reported as an adverse event. There is no need to report as an adverse event if the abnormal test result was caused by an error.

Women of childbearing age aside from subjects with confirmed sterilization operation and menopause (Includes surgical menopause) shall be checked for pregnancy through urine hCG test during visit 1 and 4.

#### **4.1.2.3 Measurement of Vital Signs and Weight**

Vital signs should be measured upon every visit and check for systolic/diastolic blood pressure and pulse in sitting position.

Weight should be measured upon every visit without jacket, shoes and with empty pockets and the scale used for measurement should be the same scale for every visit if possible.

#### **4.1.2.4 Physical Examination**

Conduct physical examination according to the clinical trial schedule. Physical examination includes exterior, head, chest/lungs, heart, abdomen, urinary/reproductive system, limbs, musculoskeletal system, nervous system, and lymphoid organs.

Significant items discovered during screening should be recorded under

physical examination on the case report and significant items in terms of physical examination opinion meeting the definition of adverse event after administration of investigational product should be recorded under adverse events on the case report. However, occurrence of symptoms and signs that are not ideal prior to administration of investigational product shall be recorded under current medical history investigation on the case report.

#### **4.1.2.5 ECG**

ECG should be conducted for all subjects during visit 1 and 4 as 12-lead ECG and normal/abnormal test results as well as clinical significance for abnormal results should be recorded in the case report. Also, ECG may be conducted selectively during the visit due to premature conclusion due to adverse effect by decision of the investigator when necessary. However, this test can be omitted if there are test results within 3 months from visit 1.

#### **4.1.2.6 X-Ray Examination**

X ray imaging shall be conducted on diseased joint area during visit 1. Test results must comply with ACR diagnosis criteria listed under Item 11.3 and there should be no opinion applicable for exclusion criteria. However, this test can be omitted if there are test results within 4 weeks from visit 1.

#### **4.1.3 Other**

##### **4.1.3.1 Demographic Survey**

Prior to clinical trial, describe the purpose and details of this clinical trial in detail to subject, receive written consent, and assign screening number according to sequence of written consent given followed by demographic survey.

Records should include written consent given, date of consent, gender, birthday, age, etc.

##### **4.1.3.2 Medical/Medication History**

Investigate and record medical history and medication history of subject through interview and review of past diagnosis records. Details included in medical history and medication history investigations are as below.

For medical history, record past and current medical history including surgical history within past year prior to participation in clinical trial as well as hypersensitivity, occurrence period (Year or month/year), and investigator opinion. Investigate disease period for osteoarthritis of the knee in detail through interview with patient.

Medication history should include medication history and administration (Administration method, dosage, administration period, etc.) within 4 weeks (2 Months for hyaluronic acid and 3 months for steroid drugs).

Compare with confirmed details from the medication history during screening to investigate any changes and record any changes in co-administered drugs in detail on the case report.

## **4.2 Procedure by Visit**

### **4.2.1 Visit 1(Screening and Washout Period, 14 Days Prior to Trial)**

Subjects selected for participation in this study shall be evaluated according to following sequence after listening to description of the study.

- 1) Describe trial procedure to subject and receive written consent form from subject prior to participation.
- 2) Assign screening number to subject in sequence of consent.
- 3) Survey and record demographic data and medical/medication history(Past and current history including surgeries).
- 4) Measure vital signs and weight and conduct physical examination.
- 5) Measure weight.
- 6) Conduct laboratory tests(Hematologic test, blood chemistry test, urine test, blood coagulation test).
- 7) Conduct pregnancy test for female subjects of childbearing age.
- 8) Perform ECG.
- 9) Conduct x-ray examination.
- 10) Evaluate according to ACR diagnosis criteria.
- 11) Evaluate according to inclusion/exclusion criteria.
- 12) Stop administration if subject is being regularly medicated with pain reliever and such and train on the washout period over 3~14 DAYS.

- 13) Evaluate 100mm Pain VAS.
- 14) Prescribe rescue drug.
- 15) Train on rescue drug log writing and distribute rescue drug log.
- 16) Schedule next visit.

#### **4.2.2 Visit 2(Random Assignment and Administration of Investigational product, Day 1)**

This visit takes place after washout period(3~14 days) for subjects administered pain relievers and such and the evaluations for this visit are as below.

- 1) Check for changes in medical/medication history compared to previous visit.
- 2) Check for washout period for pain reliever, etc.
- 3) Measure vital signs and weight and conduct physical examination.
- 4) Evaluate 100mm Pain VAS.
- 5) Combine all examination and evaluation results including clinical lab results up until this point and perform final evaluations whether qualified subjects according to inclusion/exclusion criteria have been selected.
- 6) Assign assignment number through random assignment.
- 7) Evaluate K-WOMAC.
- 8) Train on administration method and distribute investigational products.
- 9) Recover residual clinical trials from the subject and record residual quantity.
- 10) Distribute new rescue drug.
- 11) Train on rescue drug log writing and distribute new rescue drug log.
- 12) Schedule next visit.

#### **4.2.3 Visit 3(Intermediary Visit, Day 14±3)**

This visit takes place on day 14 after initial administration of investigational products and evaluates the following items.

- 1) Check for changes in co-administered drugs compared to previous visit.
- 2) Investigate for occurrence of adverse events and its details.
- 3) Measure vital signs and weight and conduct physical examination.
- 4) Evaluate 100mm Pain VAS.
- 5) Evaluate K-WOMAC.

- 6) Evaluate Patient Global Assessment.
- 7) Train on administration method and distribute investigational products.
- 8) Recover residual clinical trials from the subject and record residual quantity.
- 9) Distribute new rescue drug.
- 10) Train on rescue drug log writing and distribute new rescue drug log.
- 11) Schedule next visit.

#### **4.2.4 Visit 4(End of Clinical Trial, Day 28±3)**

This visit takes place on the last day of the study for final effectiveness evaluation of subjects administered investigational products for 28 days. Also, the following items are evaluated even if the clinical trial ends prematurely.

- 1) Check for changes in co-administered drugs compared to previous visit.
- 2) Investigate for occurrence of adverse events and its details.
- 3) Measure vital signs and weight and conduct physical examination.
- 4) Conduct laboratory tests(Hematologic test, blood chemistry test, urine test).
- 5) Conduct pregnancy test for female subjects of childbearing age.
- 6) Perform ECG.
- 7) Evaluate 100mm Pain VAS.
- 8) Evaluate K-WOMAC.
- 9) Evaluate Patient Global Assessment.
- 10) Recover residual clinical trials from the subject and record residual quantity.

#### **4.2.5 Unscheduled Visit**

Additional visits aside from scheduled visits may take place at the request of subject or subject's representative or by decision of the investigator when necessary.

## **5. SUBJECT SELECTION AND DROPOUT CRITERIA**

### **5.1 Inclusion Criteria**

Patients meeting the following conditions are selected as subjects.

1. Male and female patients between age 35~80
2. Patients diagnosed with osteoarthritis of the knee according to ACR diagnosis criteria with Kellgran & Lawrence stage I~III diagnosis on x-ray imaging
3. Patients evaluated with osteoarthritis to be stable for 3 months prior to clinical trial by clinical physician
4. Patient with at least 40mm on 100mm Pain VAS scale during visit 2
5. Patients who voluntarily gave consent in written form to participate in this clinical trial

### **5.2 Exclusion Criteria**

Patients meeting following conditions are excluded from subjects.

1. Patient with secondary osteoarthritis
2. Patient suffering from disease that may affect the effectiveness assessment such as bursitis, tenosynovitis, fibromyalgia syndrome, rheumatoid arthritis, and other inflammatory joint disease
3. Subject with confirmed with an ulcer or stomach disease through gastroscopy
4. Patient with history of invasive knee joint operation, knee joint injury, arthroscopic joint operation within 12 months prior to screening visit or patient scheduled operation during clinical trial period
5. Patient with history of artificial joint surgery for knee joint
6. Patient with malignant tumor(However, patient without remission within 5 years after completion of treatment can be registered)
7. Patient with regular administration of psychoactive drug or narcotic analgesic which may affect sense of pain for at least 3 months
8. Subject administered with glenoid cavity injection or systemic injection(Oral administration or absorption of corticosteroid for 1 day exceeding 1500 $\mu$ g) of steroid within 3 months prior to screening visit

9. Subject with hyaluronic acid injection for knee joint within 2 months prior to screening visit
10. Subject with intercurrent disease or medicated with co-administered drugs that are prohibits prescription of non-steroid anti-inflammatory pain reliever
11. Patient with history of asthma, hives, and allergic reaction against aspirin or other non-steroid anti-inflammatory pain reliever(COX-2 inhibitor included)
12. Patient requiring treatment for pain before and after CABG
13. Patient with inherited galactose intolerance, lapp deficiency, or glucose-galactose malabsorption
14. Patient with inflammatory bowel disease such as Crohn's disease or ulcerative colitis
15. Patient with severe renal disorder
16. Patient with severe liver disorder
17. Severe uncontrollable high blood pressure(Systolic blood pressure $\geq$ 160mmHg, diastolic blood pressure $\geq$ 100mmHg)
18. Patient with clinically significant systemic disease such as hematologic, heart(Congestive heart failure, ischemic heart disease, etc.), lung, nervous disease
19. Patient who does not consent for birth control\* method permitted for this clinical trial among female subjects that may become pregnant during clinical trial period  
 \*Medically permitted birth control method: Condom, usage of intravenous and inserted contraceptive, installation of birth control device within the vagina, oral birth contraceptive
20. Subjects with dependency of drugs or alcohol
21. Other patients disqualified by the researcher

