| Exclusion Criteria | 

1. Patient with secondary osteoarthritis

2. Patient suffering from disease that may affect the effectiveness assessment such as bursitis, tenosynovitis, fibromyalgia syndrome, rheumathritis, and other inflammatory joint disease

3. Subject with confirmed with an ulcer or stomach disease through gastroscop

4. Patient with history of invasive knee joint operation, knee joint injury, arthroscopic joint operation within 12 months prior to screening visit or patient scheduled operation during clinical trial period

5. Patient with history of artificial joint surgery for knee joint

6. Patient with malignant tumor(However, patient without remission within 5 years after completion of treatment can be registered)

7. Patient with regular administration of psychoactive drug or narcotic analgesic which may affect sense of pain for at least 3 months

8. Subject administered with glenoid cavity injection or systemic injection(Oral administration or absorption of corticosteroid for 1 day exceeding 1500<math>\mu</math>g) of steroid within 3 months prior to screening visit

9. Subject with hyaluronic acid injection for knee joint within 2 months prior to screening visit

10. Subject with intercurrent disease or medicated with co-administered drugs that are prohibits prescription of non-steroid anti-inflammatory pain reliever

11. Patient with history of asthma, hives, and allergic reaction against aspirin or other non-steroid anti-inflammatory pain reliever(COX-2 inhibitor included)

 |

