- (3) Patient with severe liver disorder
- (4) Patient with severe renal disorder
- (5) Patient with severe cardiac insufficiency
- (6) Patient with severe high blood pressure
- (7) Patient with hypersensitivity to substance of this drug
- (8) Patient exhibiting asthma, hives, allergic reactions, and such medical history towards aspirin and other non-steroid anti-inflammatory pain reliever(Includes COX-2 inhibitor)(Critical anaphylactoid reactions have been rarely reported after administration of non-steroid anti-inflammatory pain reliever in such patients)
- (9) Treatment for pain before and after CABG
- (10) Breastfeeding woman
- (11) This drug contains lactose and it should not be administered to patients with inherited galactose intolerance, lapp deficiency, or glucose-galactose absorption disorder.

3. Administer with caution to following patients

- (1) Patient with history of peptic ulcer
- (2) Patient with abnormal blood levels of such medical history
- (3) Patient with tendency to hemorrhage(May exhibit platelet function disorder)
- (4) Patient with liver disorder of such medical history
- (5) Patient with renal disorder or such medical history
- (6) Patient with heart disorder
- (7) Patient with high blood pressure
- (8) Patient with medical history of hypersensitivity
- (9) Patient with bronchial asthma
- (10) Patient with SLE and MCTD

(11) Patient with ulcerative colitis

(12) Patient with Chron's disease

(13) Elderlies and children

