#### 8. Administration for breastfeeding women

Lactic transfer has been reported in animal test(Rat) so this drug should not be administered while breastfeeding.

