## 2. Do not administer to following patients

- (1) Patient with active peptic ulcer/hemorrhage or such medical history
- (2) Patient with hypersensitivity to this drug or its ingredients or other drugs(Diclofenac) of same group
- (3) Patient exhibiting asthma, hives, allergic reactions, and such medical history towards aspirin and other non-steroid anti-inflammatory pain reliever(Includes COX-2 inhibitor)(Critical anaphylactoid reactions have been rarely reported after administration of non-steroid anti-inflammatory

pain reliever in such patients)

- (4) Patient with asthma exposed to risk of increase in asthma severity, hives, or acute rhinitis due to aspirin or other drugs inhibiting other prostaglandin compounds
- (5) Treatment of pain before and after CABG
- (6) Patient with severe cardiac failure
- (7) Patient with severe renal disorder
- (8) Patient with severe liver disorder
- (9) Patient with medical history of gastrointestinal tract hemorrhage or perforation due to non-steroid anti-inflammatory pain reliever
- (10) Pregnant woman in late stage of pregnancy
- (11) Breastfeeding woman
- (12) Patient with inflammatory intestinal disease such as Chron's disease or ulcerative colitis
- (13) Patient with hemorrhage or blood coagulation disorder

3. Administer with caution to following patients

- (1) Patient with renal disorder or such medical history
- (2) Patient with fluid retention or cardiac failure
- (3) Patient administered diuretic or ACE inhibitor
- (4) Patient in recovery period after surgical treatment
- (5) Elderly
- (6) Patient with bronchial asthma or such medical history(Bronchospasm has been reported as result of administering non-steroid anti-inflammatory pain reliever)
- (7) Patient with inherited porphyrin metabolism disorder
- (8) Patient with high blood pressure
- (9) Patient with liver disorder or such medical history
- (10) Patient with medical history of digestive tract ulcer due to long term administration of non-steroid anti-inflammatory pain reliever who requires long term administration of this drug and being treated for digestive ulcer with misoprostol and such(There are digestive ulcers resistant to misoprostol treatment so observe progress while administering this drug.)
- (11) Women that may be in early or intermediate pregnancy stage, women that may be pregnant, or women that are planning for pregnancy
- (12) Patient administered anticoagulant

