## 7. Administration for pregnant and breastfeeding women

- (1) There is no clinical data on administration of this drug for pregnant women. Administration of this drug may prematurely shut down the arterial tube of the embryo towards late stage of pregnancy like other non-steroid anti-inflammatory pain reliever so this drug should be administered at minimum dosage with caution for women planning for pregnancy or in early/intermediate stage of pregnancy and administration of this drug should be restricted for pregnant women in late stage of pregnancy(Last trimester).
- (2) Safety for pregnant women has not been sufficiently established with current data. Test on rats for this drug revealed increased frequency of dystocia like other drugs that inhibit synthesis of prostaglandin as well as

delay in childbirth and decrease in survival of newborn.

- (3) Safety for breastfeeding women has not been sufficiently established with current data and it is not yet known whether this drug is secreted to breastmilk of human. However, many drugs not only transfer to breastmilk but there are also risks of severe adverse events for babies so breastfeeding or administration of this drug should be stopped considering the importance of drug administration for breastfeeding women.

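### Section 5.2 does not name breastfeeding, which 11.1 contraindicates for both study drugs, and only partly covers Airtal's bars on past ulcer and NSAID-related GI bleeding or perforation

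*Protocol*

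**What the plan says.** Exclusion 3 in section 5.2 is the criterion aimed at ulcer and stomach disease: "Subject with confirmed with an ulcer or stomach disease through gastroscopy". The synopsis has the same item. Exclusion 10 covers intercurrent disease or co-medication that rules out an NSAID. Exclusion 14 covers inflammatory bowel disease. Exclusion 19 concerns women who could become pregnant and refuse contraception. Exclusion 21 leaves other exclusions to the investigator's judgement.

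Appendix 11.1 sets out, drug by drug, who must not receive the product.

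- Airtal (11.1.2, part 2), item 1: "Patient with active peptic ulcer/hemorrhage or such medical history".
- Airtal, item 9: "Patient with medical history of gastrointestinal tract hemorrhage or perforation due to non-steroid anti-inflammatory pain reliever".
- Airtal, item 11, and Pelubi CR (11.1.1, part 2), item 10: "Breastfeeding woman".
- Pelubi CR, part 8, repeats the last bar, citing transfer into milk in rats: "so this drug should not be administered while breastfeeding".

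The two drugs differ on GI history. For Pelubi CR, "Patient with history of peptic ulcer" is on the list of patients to be treated with caution (11.1.1, part 3, item 1), not on the contraindication list. Both drugs' general cautions (11.1.1, part 5, item 7; 11.1.2, part 5, item 2) ask for great care, without a ban, in patients with ulcer disease or past GI haemorrhage.

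**The concern.** Allocation is double-blind and 1:1 (section 3.1), so everyone randomised must be fit for either drug. The eligibility list therefore has to carry the contraindications of both products. It does so for most of them, which makes the missing ones look like an oversight.

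Two groups can pass the listed criteria although the appendix says not to treat them. The first is breastfeeding women. The second is patients with a past ulcer, bleed or perforation that bars Airtal but was never confirmed by gastroscopy, or that lies outside the ulcer and stomach category. The final eligibility check at Visit 2 (4.2.2, item 5) is made against the inclusion and exclusion criteria, and that is where the gap lies.

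What is at stake is patient safety. The appendix itself puts the risk of GI haemorrhage on an NSAID at more than 10 times higher in patients with ulcer disease or past GI bleeding than in those without.

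**Working it through.** The plan gives no figure to reproduce, so the check sets each contraindication list beside the 21 exclusions in 5.2.

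**Airtal (11.1.2, part 2), 13 items**

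| Items | Counterpart in 5.2 | Status |
|---|---|---|
| 2, 3, 4 (hypersensitivity, aspirin/NSAID allergy, asthma) | Exclusion 11 | matched |
| 5 (CABG) | 12 | matched |
| 6, 13 (cardiac failure, bleeding/coagulation disorder) | 18 | matched |
| 7 (renal) | 15 | matched |
| 8 (liver) | 16 | matched |
| 12 (inflammatory bowel disease) | 14 | matched |
| 1, 9 (ulcer/haemorrhage, active or past; NSAID-related bleed or perforation) | 3 | in part |
| 10 (late pregnancy) | not named; Visit 1 urine hCG, 4.1.2.2 | caught by test |
| 11 (breastfeeding) | none | unmatched |

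Total: 9 matched + 2 in part + 1 by test + 1 unmatched = 13.

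**Pelubi CR (11.1.1, part 2), 11 items**

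| Items | Counterpart in 5.2 | Status |
|---|---|---|
| 1 (current peptic ulcer) | 3 and 10 | matched |
| 2, 5 (blood abnormality, cardiac insufficiency) | 18 | matched |
| 3 (liver) | 16 | matched |
| 4 (renal) | 15 | matched |
| 6 (hypertension) | 17 | matched |
| 7, 8 (hypersensitivity, NSAID allergy) | 11 | matched |
| 9 (CABG) | 12 | matched |
| 11 (lactose-related disorders) | 13 | matched |
| 10 (breastfeeding) | none | unmatched |

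Total: 10 matched + 1 unmatched = 11.

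Combined: 19 matched + 2 in part + 1 by test + 2 unmatched = 24. The two unmatched items are the same condition, once on each list. "Matched" here means matched in substance, not word for word.

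**Breastfeeding.** Exclusion 19 is about contraception. The hCG test detects pregnancy, not lactation. Breastfeeding is neither an intercurrent disease nor a co-medication, so exclusion 10 does not reach it. Women are eligible from age 35 (5.1), so the case is possible.

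**GI history.** Exclusion 3 has no time limit, so it can reach a past ulcer or stomach lesion, but only one confirmed by gastroscopy. Gastroscopy appears neither in the trial schedule nor among the Visit 1 procedures (4.2.1). Exclusion 10 speaks of intercurrent disease, which on its natural reading is not a resolved event. What stays uncovered is a past ulcer or bleed never confirmed by gastroscopy, and an NSAID-related bleed or perforation outside the ulcer and stomach category.

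**Consequence under 1:1 allocation.** For a breastfeeding entrant, the chance of a contraindicated drug is 1/2 + 1/2 = 1. For an entrant with uncovered GI history, the contraindication is Airtal's alone, so the chance is 1/2. If k such patients entered, k/2 would be expected to receive Airtal.

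**The case against.** The strongest reply is that 5.2 already offers a way out. Exclusion 21 lets the investigator disqualify other patients. It is one of the criteria checked at Visit 2, and the appendix that gives grounds for using it is part of the protocol. Section 9.4 also asks for strict evaluation of eligibility, and section 5.3 allows withdrawal. This stands as far as it goes: a reader might infer that nothing in 5.2 can stop such a patient, and that is not so. But exclusion 21 permits refusal without requiring it. It cannot ensure the same decision at 9 institutions, and on the same reasoning exclusions 11 to 16 would not be needed either.

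The second reply is that the gap is narrow. Breastfeeding will be rare among patients aged 35 to 80 with knee osteoarthritis. Airtal's own text on lactation offers a choice ("breastfeeding or administration of this drug should be stopped considering the importance of drug administration for breastfeeding women"), so a woman who stopped breastfeeding would satisfy it. On GI history, exclusion 3 already catches gastroscopy-confirmed disease, and the translated wording of exclusion 10 might be stretched to some past events. All of this limits the number affected. None of it allows breastfeeding and treatment together, or brings an unconfirmed past bleed clearly within a listed criterion.

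Two stronger readings are tempting and fail.

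- A reader might infer that screening looks back only one year and so misses older bleeds. In 4.1.3.2 the one-year limit attaches to surgical history, and 4.2.1 item 3 asks for past and current history without a limit.
- A reader might infer that any past GI haemorrhage, whatever its cause, must be excluded. Beyond Airtal's items 1 and 9, both drugs' texts ask only for caution.

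**Conclusion.** The mismatch is real and should be corrected. Breastfeeding is contraindicated for 2 of 2 study drugs and named in 0 of 21 exclusions. Airtal's items 1 and 9 are covered only in part. A patient whom the appendix says not to treat can pass the listed criteria unless the investigator chooses to use exclusion 21.

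The practical size is small. The protocol gives no figure for how many candidates are affected, and the count of list items says nothing about it. That breastfeeding candidates will be few is an inference from the age range and the disease. The GI half rests on reading intercurrent disease in exclusion 10 as current, not resolved, disease. The breastfeeding half rests on no such reading. Sample size, the non-inferiority test and the primary analysis are unaffected.

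**What to change.** Add two exclusions to 5.2 and the synopsis:

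- breastfeeding women;
- active or past peptic ulcer or haemorrhage, or a history of gastrointestinal haemorrhage or perforation due to NSAIDs.

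The second line follows Airtal's items 1 and 9 and should go no wider. Both can be checked from the medical history already taken at Visit 1, so no new test or visit is needed.

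The cost is an amendment to the wording and the loss of a few candidates. Some of these would carry only a caution for Pelubi CR. Their exclusion follows from blinded allocation, because they could equally be given Airtal. No statistical figure in the plan has to change.
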